#### Maintenance/boosters across the three components

Specific elements were designed to support maintenance of the changed behaviours, listed below under each of the components. For each intervention school, a *Let’s Move It school team* is founded, composed of voluntary teachers and the Let’s Move It project coordinator as their contact person. It function is to cover all these elements and aim at increasing generalisability, sustainability, and maintenance of the Let’s Move It intervention.One *booster session* is delivered over the following 3-6 months to support maintenance of the changes. Students are invited to follow Let’s Move It *social media* channels with regular “boosters” (e.g., pictures of Let’s Move It posters, suggestions for seasonal PA in the area). *Posters* and table triangle stands are still visible in schools after the intensive intervention until the end of the trial.The third *workshop* for the teachers is scheduled after the intensive 2-month intervention period. Two quarterly *email newsletters* are sent to teachers to remind of the importance of and strategies for sitting reduction. Additionally, school heads/educational track directors are requested to discuss the Let’s Move It activities in *teacher meetings as part of the agenda* (slideshow materials and discussion questions are provided to them). A teacher tailored *year-long calendar poster* is placed at the wall of the teachers’ staff office to remind of the various sitting reduction activities teachers selected in the workshops to use throughout the year. Enthusiastic teachers and other staff members are invited to affiliate with the school team that enhances maintenance of intervention activities in schools after the 2-month intensive intervention (e.g., recycling posters, raising the question of sitting reduction in staff meetings).The school team is requested to ensure continued high access to sports facilities. The use of online videos is promoted in the face-to-face booster session and posters.

A central element across all intervention is autonomy supportive interaction designed to foster self-determined motivation in both students and teachers, aiming for sustained motivation and behaviour (Table 1). Active learning techniques and gradual, step-wise progress, with a celebration of even small changes is emphasised. Sample posters and other materials are shown in the Additional file 1. Intervention components and their development are described more fully elsewhere [19].

It should be noted that the intervention pertains to both the class cluster level (e.g. Let’s Move It student sessions, teacher-led activity breaks in classes) and individual level (e.g. tailored goals and action plans), as well as school cluster level (poster campaign, teachers’ workshop & PA equipment, school team). All students of the included classes participate in the Let’s Move It sessions as part of their normal curriculum, i.e., the voluntariness involves participation in the research measurements.

#### Control condition

Control group students receive teaching as usual, i.e., standard curriculum. Whereas the feasibility trial control group received leaflets informing of consequences of PA and SB, the main trial uses standard school curriculum as the comparison, because 1) comparison to standard only provides more relevant information and 2) the leaflets were perceived unfeasible [20].

#### Strategies for enhancing and monitoring intervention fidelity

The intervention sessions are carefully manualised. All intervention facilitators are carefully trained, with role-play exercises and ongoing revisions. Intervention facilitators keep track of components delivered, as well as the quality of delivery (e.g., interaction elements), by filling in a self-assessment form after each session, to assess whether the intervention was delivered as intended and to ensure high fidelity. We evaluate the extent to which opportunities to access community and school PA facilities were enhanced, and the fidelity of poster campaign uptake and maintenance. We assess receipt and use of intervention materials (e.g., use of workout and activity break videos) and enactment of the BCTs taught in intervention classes [31].

### Primary outcomes

In line with intervention targets, primary outcomes are, for PA, changes in MVPA and for SB, changes in overall sedentary time and breaks in sedentary time. These are designed to capture key aspects of the behaviours. The objectively measured PA and SB outcomes are based on accelerometry [32]. Self-reported MVPA outcome is needed to measure types of PA that accelerometry does not (e.g., water sports, contact sports not allowing for any attachments to body).

### Secondary outcomes and process evaluation

Secondary outcomes among students include objectively measured body composition (muscle and fat mass), other indicators of activity (e.g. self-reported SB), physical and mental well-being, and psychosocial variables (e.g. behavioural automaticity). Key secondary outcomes among teacher participants include self-reported sitting reduction activities and observed student behaviour.

In order to examine mechanisms of change and implementation fidelity, processes will be evaluated using both quantitative and qualitative methods. Evaluated process variables include hypothesised mediators, including psychological theoretical determinants, BCT use, observed teacher sitting reduction behaviours. Intervention fidelity, responses to intervention and effectiveness in subgroups will also be investigated.

### Sample size

The internal pilot study data (the first and second batches) were subject to interim analysis in line with the analysis plan to investigate whether the assumptions for the initial power calculations were correct (e. g., intra-cluster correlation and standard deviations for changes in outcomes). This was done in order to make adjustments to the data collection plan, to avoid collecting too much or too few data. Additionally, accumulation of accelerometry data was investigated. Altogether 502 participants (96 % of total potential) consented to the measurements. Three hundred seventy six participants were delivered the accelerometer, and of these, 267 (71 %) wore the accelerometer device over 10 h of data on at least four days. Descriptive data from the internal pilot study is presented in Additional file 2: Table S1.

We conducted power analyses for all primary outcome measures. For individual-level design, a sufficient number is 176 persons per arm to determine a change of effect size d = 0.30 (e.g. a mean of 8.24 min difference in daily MVPA or 33.44 min difference in daily sedentary time) with 80 % power and an alpha of 5 %, translating to a post-dropout sample size of 352.

Individuals in this trial are nested within clusters (classes) when the intervention is delivered, which may affect the results. Therefore we also calculated the effect of clustering on the power, with a method [33] that took into account the intracluster correlation coefficient (ICC), varying cluster sizes and the expected effect. Data from the internal pilot was used to estimate the ICC and assess the likely mean and SD of cluster sizes. The ICC for MVPA in the internal pilot study varied from 0.033 (self-report measure) to 0.059 (objective measure) and we used a mean cluster size of 17 (SD = 3.83). This resulted in design effects of 1.56 and 2.00, giving us 80 % power to detect d = 0.3 with a sample sizes of 549 and 703, for self-report and objective MVPA measures, respectively. Using the same cluster parameters for the SB measures, with ICC of 0.012 for interruptions to sitting and 0.057 for sedentary time, design effects of 1.21 and 1.96 point to requirements of 425 and 691 students, respectively.

Drop-out rates in previous similar trials [9] with sample totalling more than 100 and containing both genders have varied widely, from 3.1 to 54.1 %. Our internal pilot study showed a dropout of ~25 % from T1 to T3. Due to improvements in follow-up data collection procedures, dropout rates are expected to diminish in batches 3–6. In conclusion, with an expected sample size of ca. 1100 students, and with a dropout of 20 % from T1 to T3 and a further 20 % from T3 to T4, we would be well-equipped to account for clustering in all primary outcome measures with the post-dropout sample size of 704. Assuming 20 % of participants are classified as high-active and therefore excluded from the MVPA analysis, we expect to achieve 93 % power to detect d = 0.3 with individual-level analyses. Due to the drop in SD, this effect translates to an absolute difference of 7.25 min for the target group, instead of 8.24 min for the whole sample. The ICC estimated from the internal pilot study for the low- to moderate-active students’ MVPA change was 0.038, leading to a design effect of 1.65 and subsequently a post-dropout sample size of 580 to reach 80 % power.

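### The 704 students said to suffice for every primary outcome are retained students, not students with valid accelerometer data. At the pilot's 71% valid wear, power at 14 months for accelerometer MVPA and sedentary time falls below the stated 80%

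*Protocol article*

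**What the plan says.** All of the following is in the protocol article, Sample size, unless another section is named.

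- **Individual-level size:** "a sufficient number is 176 persons per arm to determine a change of effect size d = 0.30", "with 80 % power and an alpha of 5 %, translating to a post-dropout sample size of 352".
- **Requirement after clustering by class:** 549 for self-reported MVPA, 703 for accelerometer MVPA, 425 for breaks in sedentary time and 691 for sedentary time.
- **Pilot accelerometry:** 502 students consented. "Three hundred seventy six participants were delivered the accelerometer", and 267 of these (71%) "wore the accelerometer device over 10 h of data on at least four days".
- **Dropout:** "Our internal pilot study showed a dropout of" about 25% from T1 to T3. Lower dropout is expected in batches 3–6 because follow-up procedures were improved. The plan then assumes 20% to T3 and a further 20% to T4, from about 1100 students.
- **Conclusion:** "we would be well-equipped to account for clustering in all primary outcome measures with the post-dropout sample size of 704".

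The section Primary outcome measures confirms that MVPA, sedentary time and breaks are taken from the accelerometer. The only primary outcome that does not need the device is self-reported MVPA.

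**The concern.** The comparison sets a count of retained students (704) against a required count of analysable records (703 and 691). The two match only if almost nobody who stays in the trial fails to produce valid wear. The same section reports that 29% of pilot students given a device did fail (109 of 376), and it says accumulation of accelerometry data was examined in order to adjust data collection. The yield was measured and reported but not carried into the conclusion.

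The Background presents objective measurement and the avoidance of an underpowered design as reasons for the trial. If the claim stands, a null result at 14 months on accelerometer MVPA or sedentary time would be read as coming from a comparison with 80% power, when the plan's own pilot figures point to less.

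**Working it through.** **Inputs (Sample size; Trial design for the 57 classes).** d = 0.30; alpha 5%, taken as two-sided; 80% power; class size 17 with SD 3.83; ICC 0.059 (accelerometer MVPA), 0.057 (sedentary time), 0.012 (breaks), 0.033 (self-reported MVPA); 1100 students; 20% then 20% dropout; 267 of 376 with valid wear; 57 classes.

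**1. The plan's own figures reproduce.** A two-sample t-test gives 176 per arm, 352 in total. The design effect is DE = 1 + ((1 + CV²) × m − 1) × ICC, with CV = 3.83/17 = 0.225.

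| Outcome | DE at m = 17 (stated) | 352 × DE (stated) |
|---|---|---|
| Self-reported MVPA | 1.556 (1.56) | 548 (549) |
| Accelerometer MVPA | 1.995 (2.00) | 702 (703) |
| Breaks | 1.202 (1.21) | 423 (425) |
| Sedentary time | 1.961 (1.96) | 690 (691) |

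Retained at T4: 1100 × 0.8 × 0.8 = 704.

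**2. Valid wear that the claim requires among the 704.** MVPA: 703/704 = 99.9%. Sedentary time: 691/704 = 98.2%. Breaks: 425/704 = 60%. Pilot: 267/376 = 71.0%.

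**3. Analysable records at the pilot yield.** T4: 704 × 0.710 = 500. T3: 880 × 0.710 = 625.

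**4. Power at d = 0.30.** With n = N/(2 × DE) per arm, power is approximately Φ(0.30 × √(n/2) − 1.96). DE is taken once at the protocol's class size of 17 and once at m = N/57, because fewer valid students per class also lowers the design effect.

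| Wave, N | m | MVPA: DE, power | Sedentary time: DE, power | Breaks: DE, power |
|---|---|---|---|---|
| T4, 500 | 17 | 1.99, 66% | 1.96, 67% | 1.20, 86% |
| T4, 500 | 8.8 | 1.48, 78% | 1.47, 79% | 1.10, 89% |
| T3, 625 | 17 | 1.99, 75% | 1.96, 76% | 1.20, 93% |
| T3, 625 | 11.0 | 1.62, 84% | 1.60, 84% | 1.13, 94% |

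Example, MVPA at T4 with m = 8.8: 500/1.48 = 337 effective, n = 168, and Φ(0.30 × √84.2 − 1.96) = Φ(0.79) = 0.79 (0.78 with the t distribution).

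**5. Detectable difference in MVPA at T4 with 80% power.** d is about 0.31 (m = 8.8) to 0.36 (m = 17), against the planned 0.30. The protocol equates d = 0.30 with 8.24 min, so this is roughly 8.4 to 9.8 min.

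**6. Yield at which the matched design effect would reach 80%.** Setting N/DE = 352 with m = N/57 for MVPA gives N = 352 × 0.941 / (1 − 352 × 1.0508 × 0.059/57) = 331.2/0.617 = 537, or 537/704 = 76% valid wear.

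**7. Dropout alone, without any accelerometer loss.** An average of 20% to T3, given 25% in the first 502, requires 880 − 502 × 0.75 = 503.5 retained of the other 598, a loss of 15.8%. If those batches lose 20% instead, T4 has (376.5 + 478.4) × 0.8 = 684 students. MVPA power is then about 79% at m = 17 and about 85% at m = 684/57 = 12.

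**The case against.** Several points on the other side have weight.

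- **The shortfall is modest on the fairer design effect.** With 500 students over 57 classes, power is 78–79%, not 66%, and 76% valid wear would restore 80% for MVPA. After the pilot, text reminders were moved earlier, and a movie voucher is offered at T4 for prompt return of the device (Strategies to ensure maximum study participation). Yield may therefore rise. The protocol puts no figure on this, and its claim as argued, at class size 17, needs almost complete wear.
- **The mixed model uses incomplete longitudinal data** (Statistical analyses), so students with valid earlier records contribute something. This stands in part, but the Sample size section argues from a post-dropout count and claims no such gain. The count of 500 also does not require a valid baseline record, although the outcome is change.
- **The wear criterion is reported as a pilot description**, not as a rule for entering the analysis. A looser rule would raise the yield, but the article gives no other figure.

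Three stronger readings are tempting, and the documents do not support them.

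- **That only 53% (267/502) will be analysable.** This would leave 704 × 0.532 = 374 at T4 and MVPA power of 53–70%. The article does not say at which wave the 376 received devices, or why the others did not. Since 376/502 is itself 75%, the non-delivery may be the same loss as the 25% dropout, which would then be counted twice. The figure is a conditional lower bound only.
- **That the plan ignores the pilot dropout.** It reports the 25% and says why it expects less. Falling to 684 causes no material shortfall.
- **That every accelerometer outcome is underpowered.** Breaks in sedentary time needs only 425 and keeps 86–89% power with 500.

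**Conclusion.** The claim of adequacy for all primary outcomes does not hold for accelerometer MVPA and sedentary time at T4. At the pilot's 71% valid wear, about 500 rather than 704 students are analysable, and power is 66–67% (class size 17) to 78–79% (57 classes). At T3 the answer depends on the design effect: about 75% to 84% for MVPA. Self-reported MVPA (549 needed, 704 retained) and, at the 71% yield, breaks in sedentary time are covered.

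This rests on four assumptions: the pilot yield carries over to later batches and to both follow-ups; valid wear is unrelated to dropout; the protocol's dropout rates hold; and clustering is counted at class level only, as in the protocol. If device delivery is a separate loss at T1, the position is worse, but the article does not establish that.

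**What to change.** Rewrite the conclusion of the Sample size section as follows.

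1. Give the expected analysable number and power separately for each primary outcome at T3 and T4, applying the pilot valid-wear yield to the accelerometer outcomes.
2. Use a design effect matched to the analysable class size (about 9 at T4 and 11 at T3) and show the class-size-17 result beside it.
3. Keep the adequacy statement for self-reported MVPA and, at the 71% yield, for breaks in sedentary time. For accelerometer MVPA and sedentary time at T4, replace it with the lower power and the detectable difference.
4. State the wave to which the 376 and 267 refer and why the remaining consenters had no device, so that the lower bound can be adopted or discarded.
5. As a minor addition, note that a 20% average loss to T3 implies about 16% in batches 3–6.

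The cost is a few sentences and a less favourable stated power. No additional students, measurements or changes to the analysis are required.

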## Abstract

**Background:**

Physical activity (PA) has been shown to decline during adolescence, and those with lower education have lower levels of activity already at this age, calling for targeted efforts for them. No previous study has demonstrated lasting effects of school-based PA interventions among older adolescents. Furthermore, these interventions have rarely targeted sedentary behaviour (SB) despite its relevance to health. The Let’s Move It trial aims to evaluate the effectiveness and the cost-effectiveness of a school-based, multi-level intervention, on PA and SB, among vocational school students. We hypothesise that the intervention is effective in increasing moderate-to-vigorous-intensity physical activity (MVPA), particularly among those with low or moderate baseline levels, and decreasing SB among all students.

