## Methods/Design

### Aims of the study

The primary aim of the trial is to determine the effectiveness of the Let’s Move It intervention on changes in students’ physical activity and sedentary behaviour over two months (post-intervention, T3) and 14 months (long-term follow-up, T4), specifically in the following primary outcome measures:Moderate-to-vigorous intensity PA (MVPA), as measured by accelerometry and self-reportSedentary behaviour: a) Sedentary time, and b) Breaks in sedentary time (accelerometry)

We hypothesise that the intervention is effective in increasing or maintaining PA and reducing SB, compared to control group, among girls and boys, both immediately and one year after the intensive intervention (i.e., 2 and 14 months from baseline).

As the trial is designed especially for adolescents with low PA at baseline, we expect to detect a significant difference in change in MVPA among students with low or moderate levels of MVPA at baseline. We also aim to examine the cost-effectiveness of the intervention, in terms of determining cost of incremental activity. Additionally, we will evaluate changes in secondary outcomes among students (e. g. other indicators of activity, body composition, physical and mental well-being, as well as psychosocial variables) and teachers. Process evaluation will be conducted to examine mechanisms of change, implementation fidelity and key components of the intervention, as well as responses and effectiveness in subgroups.

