### Interventions

#### Active arm: intervention overview

The intervention objective is to increase total PA, more specifically: 1) increase moderate-to-vigorous intensity PA (MVPA), especially among those with low levels of PA, 2) decrease time spent in SBs, and 3) increase the number of breaks in SB. The intervention design was preceded by a comprehensive needs assessment and preliminary research among the target group [19] as well as by synthesis of prior evidence [9] and a randomised acceptability and feasibility (rehearsal) trial [20]. The program was designed specifically for those with low or moderate baseline PA levels: The student panel for the initial development of programme purposefully consisted of youth reporting low levels of PA, and after the feasibility trial, the feedback for optimization was collected among participants excluding those with already high levels of PA. Nevertheless, Let’s Move It intervention is delivered as a universal intervention for all students, in order to minimise the risks of inequalities in accessing the intervention and any potential for stigma in case the intervention would only be targeting a subgroup within the school. The design process of the Let’s Move It intervention made sure that this intervention could fit into the school curriculum. The intervention is based on theoretical and empirical insights from behavioural science: e.g. self-determination theory [23], especially its goal content and organismic integration theories, self-regulation and planning theories [24, 25], and habit formation [26], taking into account group motivational interviewing principles for the delivery of the actual intervention activities and active ingredients [27–29].

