### Statistical analyses

Effectiveness analyses will be conducted according to the intention-to-treat principle. Primary and secondary outcomes will be analysed using generalised linear mixed model (GLMM) that will allow to take into account correlations between observations. These methods also allow the incorporation of incomplete longitudinal data into the analysis. Additional sensitivity analysis using the “as treated” approach will be conducted in order to gauge efficacy. Process analyses will include e.g. multiple mediation models to test whether the impact of the intervention is explained by its effect on the hypothesised mediators. We will conduct the outcome analyses separately for gender and different levels of baseline activity. When allowed by time and funding resources, we will also conduct the analyses by educational track, parental SES, and baseline body composition. Quantitative analyses will be conducted using the R, SPSS and the Mplus statistical softwares.

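### Two MVPA analysis populations are stated and neither is ranked as primary; separate analyses by activity level cannot show a larger effect in less active students

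*Protocol article*

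**What the plan says.** **Whole sample.** Aims of the study in the protocol article makes MVPA a primary outcome and states: "We hypothesise that the intervention is effective in increasing or maintaining PA and reducing SB, compared to control group, among girls and boys". No limit on baseline activity is attached. The intervention overview says the programme "is delivered as a universal intervention for all students". The Sample size section powers MVPA for d = 0.3, equated with 8.24 min of daily MVPA, and arrives at 549 students (self-report) and 703 (accelerometry). Statistical analyses says: "Effectiveness analyses will be conducted according to the intention-to-treat principle". It mentions no exclusion.

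**Restricted sample.** Later, the Sample size section takes 20% of students to be "classified as high-active and therefore excluded from the MVPA analysis". Separate figures follow for that set: 93% individual-level power, an effect of 7.25 min, an ICC of 0.038, a design effect of 1.65 and 580 students after dropout.

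**Effect by baseline activity.** The abstract hypothesises an MVPA increase "particularly among those with low or moderate baseline levels". Aims of the study words the expectation more narrowly: "we expect to detect a significant difference in change in MVPA among students with low or moderate levels of MVPA at baseline". The stated method is: "We will conduct the outcome analyses separately for gender and different levels of baseline activity". No interaction between arm and baseline activity is named.

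**The concern.** There are two separate weaknesses.

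First, the article contains two MVPA analyses, each with its own population, ICC, sample size and effect in minutes. Both can be read as the primary one. Without a ranking, either could be reported as the trial's MVPA result after the data are seen. If they disagree, the protocol does not say which one answers the primary question.

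Second, the abstract's hypothesis compares strata: it expects a larger effect in less active students. Separate analyses estimate an effect within each stratum but do not test whether the effects differ. The strata are very unequal (about 80% and 20%), so significance in the large one and none in the small one is a common outcome even when the effect is identical. Read as confirmation, that pattern would support a claim that the programme works mainly in its target group without evidence of any difference.

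**Working it through.** **Inputs, all from the Sample size section.** d = 0.30; alpha 5% (taken as two-sided, since the sidedness is not stated); 176 per arm, 352 in total; mean cluster size 17, SD 3.83; ICC 0.059 (objective MVPA), 0.033 (self-report) and 0.038 (low/moderate-active); 1100 students with 20% dropout twice; 20% high-active. The 57 classes come from Trial design.

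**Reproducing the plan's figures.**
- Post-dropout sample: 1100 × 0.8 × 0.8 = 704, as stated.
- Design effect = 1 + ((CV² + 1)m − 1) × ICC, with m = 17 and CV = 3.83/17. This gives 1.556, 1.995 and 1.641, against the stated 1.56, 2.00 and 1.65.
- Required N: 352 × 1.56 = 549; 352 × 1.995 = 702 (stated 703); 352 × 1.65 = 581 (stated 580).
- After the exclusion: 704 × 0.8 = 563. Power = Φ(0.3 × √(563/4) − 1.96) = 94.5%, against the stated 93%.

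The sample-size arithmetic is sound.

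**The two populations side by side.**

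| | Whole sample | High-active excluded |
|---|---|---|
| Expected N after dropout | 704 | 563 |
| Effect at d = 0.3 | 8.24 min | 7.25 min |
| Implied SD (effect/0.3) | 27.5 min | 24.2 min |
| Stated design effect | 2.00 (objective) | 1.65 |
| Stated N for 80% power | 703 | 580 |
| Clustered power at expected N | 80.4% | 79.1% |

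The 563 falls short of 580 by a trivial amount. Under a uniform d = 0.3 the two analyses have nearly the same power, so power does not settle which is primary.

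**When the choice changes the answer.** Suppose the 7.25 min benefit exists only in the less active 80%. The whole-sample difference is 0.8 × 7.25 = 5.8 min, and d = 5.8/27.47 = 0.21. With 704 students and a design effect of 2.00, power = Φ(0.211 × √(352/4) − 1.96) = 51%. The restricted analysis keeps its 79%. Opposite verdicts from the two populations are then quite possible.

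**Separate analyses under an identical effect.** Let d = 0.3 hold in both strata (563 and 141 students). The chance of significance in low/moderate but not in high-active students is power(low/moderate) × (1 − power(high)), treating the strata as independent. The document gives a design effect only for the low/moderate set (1.65), so the rest are assumptions and a range is shown:

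| Design effect, low/moderate | Design effect, high-active | Power, low/moderate | Power, high-active | Chance of the pattern |
|---|---|---|---|---|
| 1.65 | 1.06 | 79% | 41% | 47% |
| 1.34 | 1.06 | 87% | 41% | 51% |
| 1.00 | 1.00 | 95% | 43% | 54% |
| 1.65 | 1.65 | 79% | 28% | 57% |
| 2.00 | 2.00 | 71% | 24% | 54% |

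The values 1.34 and 1.06 come from students per class in each stratum with ICC 0.038: 1 + (563/57 − 1) × 0.038 and 1 + (141/57 − 1) × 0.038.

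**What a direct test could detect.** For the difference between the stratum effects, SE = √(DE × (4/563 + 4/141)), assuming a common SD and design effect (DE):

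| DE | Power for a difference of d = 0.3 | Difference detectable with 80% power |
|---|---|---|
| 1.00 | 36% | d = 0.53 |
| 1.65 | 24% | d = 0.68 |
| 2.00 | 20% | d = 0.75 |

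**The case against.** The strongest reply is that nothing is hidden. The abstract, the Background, the Aims and the intervention overview all name students with low or moderate activity as the MVPA target. The Sample size section sets that target group against the whole sample and powers both. On this reading the sentence about exclusion is loosely worded and only introduces a second, pre-declared analysis. That is plausible, and it limits the charge. It does not remove it, because the sentence refers to the MVPA analysis as such and no section says which of the two results comes first.

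A reader might infer that dropping high-active students breaches intention-to-treat. The documents do not support that. Restricting by a baseline measure and analysing students as randomised is compatible with the principle. The fault is the missing ranking.

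On the second part, the narrower expectation in the Aims, a significant difference within low/moderate students, can be tested by an analysis of that stratum alone. Only the abstract's wording is comparative. The protocol also does not say that it will infer a differential effect by comparing p-values. An analysis plan that is not shown may add an interaction. What stands is that the one method the article does state for baseline activity cannot support the abstract's hypothesis.

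Two further inferences go too far. One extends the argument to gender, but no larger effect in one gender is hypothesised, so separate gender results contradict no trial hypothesis. The other is that students without valid accelerometry could not be classified as high-active. The article does not say how that class is defined, self-reported MVPA is also collected at baseline, and the definition may properly sit in the analysis plan.

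**Conclusion.** The point holds in two parts. The article fixes two MVPA populations, 704 and 563 students after dropout, and ranks neither. If the benefit is confined to the less active 80%, clustered power is about 51% in one and 79% in the other, so the reported conclusion could depend on which is chosen. Separately, the abstract's comparative hypothesis is not tested by separate analyses. Under one common effect of d = 0.3 they would suggest a differential effect about half the time (47% to 57%).

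These figures assume a two-sided 5% level, a normal approximation and independent strata. Except for the stated 1.65 and 2.00, the stratum design effects are assumed. The strata share classes and schools, so the percentages are approximate, but the conclusion does not depend on a particular row. No error in the sample-size arithmetic and no breach of intention-to-treat is claimed.

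**What to change.** 1. Reconcile Aims of the study, Sample size and Statistical analyses by naming one primary MVPA population. All consenting students fits the overall hypothesis, the whole-sample power calculation and the absence of any exclusion in the analysis section. Choosing the target group instead would also be coherent if it were declared throughout.
2. Make the other population a named secondary estimate with a stated rank, and reword the exclusion sentence to match.
3. Add an arm by baseline-MVPA interaction to the planned mixed model, preferably with baseline MVPA continuous. Report the effects at low, moderate and high activity with intervals, and claim a larger effect in less active students only from the interaction.

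The cost is a few sentences and one model term, with no new data. The drawback is low power: about 20% to 36% for a difference of d = 0.3 when low/moderate is compared with high-active. The differential claim may therefore remain unproven, and the report should then say so.
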